### Analysis

An overview of the planned analyses for the POPPI trial is provided below. The full
statistical analysis plan will be submitted for publication ahead of database
lock.

#### Clinical evaluation

The primary analysis for the clinical evaluation will determine if there is a
significant difference in the mean PSS-SR at 6 months between patients
recruited during the intervention period at intervention sites compared with
patients recruited at control sites using a generalised linear mixed model (GLMM)
at the individual patient level (patients nested within sites and time periods)
including a random effect of site and a fixed effect of period (baseline or
intervention), and adjusted for site-level factors included within the restricted
randomisation algorithm.

For the primary outcome, the link function will be the identity link (ie, linear
regression) and standard errors will be estimated using a jackknife variance
estimate, which has been demonstrated in simulation studies to maintain the size
of the test.^33^

A secondary analysis will adjust for prespecified baseline factors associated with
poor psychological outcome (eg, sedation) and ability to resource and deliver the
intervention (eg, size of critical care unit, teaching status) at both patient and
site levels. Results of GLMMs will be reported as differences in means, 95% CIs
and P values.

Analyses of secondary outcomes will be conducted using GLMMs, with the identity
link (ie, linear regression) for continuous secondary outcomes, reported as
differences in means, and the logit link (ie, logistic regression) for binary
secondary outcomes, reported as ORs.

The above analyses will evaluate the effectiveness of the intervention among all
patients meeting the inclusion criteria and consenting to follow-up, based on the
intention-to-treat principle. A further secondary analysis will use structural
mean models with an instrumental variable of allocated treatment to estimate the
efficacy (adherence-adjusted causal effect) of the stress support sessions among
those patients consenting to psychological assessment and stress support sessions,
assessed as being at high risk of psychological morbidity and receiving stress
support sessions.^34^

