#### Economic evaluation

A cost-effectiveness analysis (CEA) will be undertaken to assess the relative
cost-effectiveness of the intervention versus usual care. Resource use and outcome
data will be used to report cost-effectiveness at 6 months and to project
the lifetime cost-effectiveness of each strategy.

The cost analysis will take a health and personal health services perspective.
Resource use data will be combined with unit costs from the NHS Payment by Results
database and from local Trust Finance Departments, to report the total costs per
patient at 6 months for intervention versus usual care.^35 36^

HRQoL data from the EQ-5D-5L questionnaires at 6 months will be combined
with survival data using linear interpolation to report QALYs at 6 months.
CEA will follow the intention-to-treat principle and report the mean (95% CI)
incremental costs, QALYs and net monetary benefit at 6 months.

CEA will use multilevel linear regression models that allow for clustering^37^ including a random effect of site and a
fixed effect of period. The analysis will adjust for prespecified baseline
covariates at both patient level and site level.

Lifetime cost-effectiveness will be projected by encapsulating the relative
effects of the alternative strategies on long-term survival and HRQoL, combining
extrapolations from the patient survival data, with external evidence on long-term
survival and HRQoL.^38 39^ The long-term
survival of patients will be extrapolated from the cluster-RCT data by fitting
alternative parametrical survival curves (eg, Weibull, exponential, lognormal, log
logistic and Gompertz) to the observed survival data. The method of parametrical
extrapolation of survival for the base case will be chosen on the basis of model
fit and plausibility when compared with age-gender matched general population
survival.^40^ Survival will then be
extrapolated according to the chosen parametrical function for the duration
of years that parametrical curves predict excess mortality compared with
the age-gender matched general population, after which we will assume that
all-cause death rates were those of the age-gender matched general population. In
the base case, quality of life calculated at 6 months will be assumed to
apply to each subsequent year of life, after allowing for decrements in quality of
life according to advancing age. We will project lifetime costs by applying
morbidity costs estimated at 6 months over the period of excess mortality.

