Predicted survival and HRQoL will be combined to report lifetime QALYs, and to
project lifetime incremental costs, incremental QALYs and incremental net benefits
for the alternative strategies of care. Sensitivity analyses will test whether the
results are robust to methodological assumptions (eg, specification of the
statistical model, extrapolation approach, alternative HRQoL assumptions and
learning curve effects).

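### The size-preserving jackknife is stated only for the primary outcome, so standard errors for the 6-month cost-effectiveness estimates, and possibly the secondary outcomes, may be too small if site effects shift between periods

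*Protocol article*

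**What the plan says.** All references are to the Analysis part of the protocol article.

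- **Primary model (Clinical evaluation).** The clustering terms are worded "including a random effect of site and a fixed effect of period (baseline or", the second of the two periods being the intervention period. The level of analysis is described separately, in the words "at the individual patient level (patients nested within sites and time periods". That nesting phrase names no second variance component, so the only stated random effect is one intercept per site.
- **Jackknife (Clinical evaluation).** The sentence that introduces it opens "For the primary outcome, the link function will be the identity link (ie, linear". The variance method comes later in the same sentence, as "regression) and standard errors will be estimated using a jackknife variance". The reason given is that this estimate keeps the size of the test.
- **Secondary outcomes (Clinical evaluation).** The text reads "Analyses of secondary outcomes will be conducted using GLMMs, with the identity". That link is meant for continuous outcomes, and the logit is used for binary ones. Neither the random effects nor the standard-error method is restated.
- **CEA (Economic evaluation).** The model is introduced by "CEA will use multilevel linear regression models that allow for clustering". Its clustering terms are then worded "including a random effect of site and a", with period entering as a fixed effect. No robust or jackknife standard error is named. Incremental costs, QALYs and net monetary benefit at 6 months are the primary economic outcomes and are reported with 95% CIs.

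**The concern.** The treatment contrast is between site-periods. Patients already recruited are excluded from re-entry, so the two periods contain different people. The baseline period lasts 5 months. The intervention period was planned at 5 to 9 months depending on the site, with 2 further months added later. A change common to all sites is absorbed by the fixed period effect. A change particular to a site is not: a model with one site intercept treats it as patient-level noise and averages it away over patients, when it averages away only over sites.

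The article itself anticipates site-specific change. The process evaluation looks for changes in unit practice since baseline at control sites and for variation in delivery across intervention sites, and the CEA sensitivity analyses mention learning-curve effects.

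At stake are intervals that are too narrow for the economic primary outcomes and, if the same model is used, false-positive rates above 5% for the secondary outcomes.

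**Working it through.** **Inputs from the Power calculation section.** There are 24 sites, 12 per group. At the review, the PSS-SR SD is 10.8 (read as within-site, which is the reading that reproduces the stated power), the ICC is 0.087 (95% CI 0 to 0.192) and the effect is 4.2 points. Patients completing follow-up per site are 12.8 in the baseline period and 16.5 in the intervention period after the extension.

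**Assumed, not in the documents.** c is the correlation between a site's effects in the two periods, taken from 0.5 to 1. The PSS-SR ICC stands in for the unknown ICCs of the secondary and economic outcomes, with 0.02 and 0.192 as a range.

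**Step 1: reproduce the plan's power.** Let s0 and s1 be the within-site variance divided by the baseline and intervention counts, and τ² the between-site variance. With one common site effect,

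Var = (1/12 + 1/12) × [s1 + τ²·s0/(τ² + s0)].

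- τ² = 10.8² × 0.087/0.913 = 11.11; s0 = 116.64/12.8 = 9.11; s1 = 116.64/16.5 = 7.07.
- Var = (7.07 + 5.01)/6 = 2.01, so SE = 1.42.
- Power = Φ(4.2/1.42 − 1.96) = 84.1% (stated 85%).
- With 12.8 patients in both periods: SE 1.53, power 78.2% (stated 78%).
- Pretrial inputs (SD 7.5, between-site SD 3, 22 per period, effect 2.9): SE 0.871, power 91.5% (stated 90%).

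All three agree within 2 points, so the design calculation also takes c = 1.

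**Step 2: let site effects shift.** The fitted model weights the baseline mean by b = τm²/(τm² + s0), where τm² is the site variance it works with. The true variance of the estimate is

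(1/6) × [s1 + τ² + b²(s0 + τ²) − 2b·c·τ²].

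The model reports (1/6) × [s1 + τm²·s0/(τm² + s0)]. What a misspecified fit estimates for τm² is not fixed in advance, so two versions are shown: (A) τm² = τ², and (B) τm² = c·τ².

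At ICC 0.087 and c = 0.8, version A has b = 0.549. The true variance is (7.07 + 11.11 + 6.11 − 9.77)/6 = 2.42, so the true SE is 1.56 against a model SE of 1.42. The ratio is 1.097. The model SE is therefore 1 − 1/1.097 = 8.8% too small, and rejection is 2 × [1 − Φ(1.96/1.097)] = 7.4%.

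| ICC | c | True/model SE (A; B) | Model SE too small by (A; B) | Rejection at nominal 5% (A; B) |
|---|---|---|---|---|
| 0.087 | 1.0 | 1.000; 1.000 | 0%; 0% | 5.0%; 5.0% |
| 0.087 | 0.9 | 1.049; 1.058 | 4.7%; 5.5% | 6.2%; 6.4% |
| 0.087 | 0.8 | 1.097; 1.113 | 8.8%; 10.2% | 7.4%; 7.8% |
| 0.087 | 0.5 | 1.227; 1.266 | 18.5%; 21.0% | 11.0%; 12.2% |
| 0.02 | 0.8 | 1.011; 1.028 | 1.1%; 2.7% | 5.3%; 5.7% |
| 0.02 | 0.5 | 1.027; 1.072 | 2.6%; 6.7% | 5.6%; 6.7% |
| 0.192 | 0.8 | 1.265; 1.271 | 20.9%; 21.3% | 12.1%; 12.3% |

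**Step 3: simulate the fitted model and the jackknife.** One simulation used 2,000 trials per setting, a REML fit with one site effect and 13 and 17 patients per site-period. The delete-one-site jackknife was computed on 500 of those trials. A second simulation used 3,000 trials. The entries are rejection rates at nominal 5%, with the jackknife referred to a normal distribution.

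| ICC | c | Model-based SE | Jackknife |
|---|---|---|---|
| 0.087 | 1.0 | 4.9% | 4.4% |
| 0.087 | 0.8 | 8.3% (second simulation 8.2%) | 4.4% (5.7%) |
| 0.087 | 0.5 | 11.5% (12.1%) | 4.0% (5.3%) |
| 0.192 | 0.8 | 12.4% | 5.4% |

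In the first simulation, at ICC 0.087, the mean model SE was 1.379 against an empirical 1.528 at c = 0.8 (10% too small), and 1.360 against 1.695 at c = 0.5 (20% too small). Both lie between versions A and B. The jackknife holds the error near 5% even though the fitted model is wrong.

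**The case against.** **The article is an overview and the full analysis plan is to follow.** The standard-error method for secondary outcomes is a detail such a plan would commonly settle, and naming the jackknife for one outcome does not exclude it for others. This stands for the secondary outcomes: their random effects and standard errors are inferred, not stated. It stands less well for the CEA, where the article does state how clustering is handled.

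**The size rests on unknowns.** The correlation is assumed, and the ICC belongs to the one outcome that is already protected. This stands in full. The true effect on other outcomes could be nil or larger than illustrated.

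**The CEA is partly covered.** Its sensitivity analyses ask whether "results are robust to methodological assumptions (eg, specification of the" statistical model), and it reports intervals without announcing a significance test. Both observations are correct. However, the sensitivity item is generic and leaves the base-case intervals as they are. Interval width is the very thing at issue in the CEA, and nothing comparable is listed for the clinical secondary outcomes.

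**A stronger reading is tempting.** A reader might infer that every model in the plan carries the flaw, that the secondary and economic standard errors will certainly be too small, or that the primary test is compromised. The documents do not support this. The secondary-outcome random effects are not given, the understatement vanishes if site effects are stable, and the jackknife protects the primary analysis.

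**Conclusion.** The point holds as a conditional one. As stated, the CEA model has no allowance for site effects that differ between periods, and the size-preserving jackknife is tied to the primary outcome. If site effects shift, model-based standard errors for the 6-month CEA estimates may be too small. The same applies to the secondary outcomes if they use the same model with model-based errors.

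The illustrated size runs from nothing at a correlation of 1, through about 9% to 10% at 0.8, to about 18% to 21% at 0.5. It is slight when the ICC is 0.02 and larger at the upper ICC limit. These figures assume a linear model, equal counts across sites, and the PSS-SR ICC in place of values the article does not give. For the binary secondary outcome they indicate direction only. The primary conclusion is not affected.

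**What to change.** State in the analysis plan, before database lock, that the leave-one-site-out jackknife (or another small-sample cluster-robust method) applies to the secondary outcomes and to the 6-month incremental costs, QALYs and net monetary benefit. Alternatively, add a site-by-period random effect to those models. The primary model needs no change.

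The cost is a sentence of wording, or one more variance component, and somewhat wider intervals for the secondary and economic outcomes. As a guide on the PSS-SR scale at ICC 0.087 and correlation 0.8, the SE with a site-by-period effect is 1.54 against a model-based 1.42. The interval is then about 1.54/1.42 = 1.08 times as wide.

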#### Randomisation

The 24 sites will be randomly assigned to either the intervention group (n=12) or
the control group (n=12), by the ICNARC CTU, using a restricted randomisation
approach to ensure balance across the groups in terms of geographical location,
hospital teaching status and size of unit. For each group of eight sites, the
individual sites will be randomised (4:4) in their second month of recruitment. It
is necessary to randomise on a cluster (‘site’), rather than
individual level to avoid contamination of usual care, as it would not be possible
to restrict parts of the intervention to individual patients.

Sites randomised to the intervention group are responsible for selecting three
POPPI nurses based on a person specification which includes:Registered nurse with ≥3 years critical care clinical
experienceEffective communicator, with patients and their families, colleagues and
collaboratorsAble to work flexiblyInterested in improving psychological care of patientsOrganised and able to manage a busy schedule

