#### Exclusion criteria

Pre-existing chronic cognitive impairment, such as dementiaPre-existing psychotic illness, such as schizophreniaPre-existing chronic PTSDReceiving end-of-life carePreviously recruited to POPPI

Patients who meet the eligibility criteria in the unit will be approached and
provided with written and verbal information about POPPI by a member of the local
research team. Potential participants will be given the opportunity to ask
questions and time to discuss the trial with family or friends before making their
decision. After the person seeking consent is satisfied that the information has
been understood and questions have been answered, they will invite the potential
participant to sign the consent form. In providing informed consent, participants
are agreeing for the trial team to have access to their medical records for data
collection and to receive a follow-up questionnaire at 6 months. In
addition, participants recruited at intervention group sites from month
6 onwards (figure 1) will be offered
the option to provide consent to receive an assessment with IPAT and subsequent
stress support sessions (if applicable). Figure 3 shows the timeline for a patient recruited at an intervention group
site from month 6 onwards.

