### Data collection

Table 1 shows the patient data
collection schedule. The following data are collected by local research teams for all
patients while in hospital:Patient details (identifiers, sociodemographics)Clinical/baseline data (date/time of critical care unit admission and
consent, eligibility criteria, quality of life score, STAI^27^ score, prior delirium (assessed by
the Confusion Assessment Method for the Intensive Care Unit (CAM-ICU),^32^ documented pre-existing anxiety or
depression)Critical care unit stay data (duration of: delirium (assessed by CAM-ICU),
sedatives, anxiolytics, anaesthetics, sleep medications, antipsychotics,
analgesics, antidepressants, vasoactive agents and mechanical
ventilation)Hospital discharge data (discharge status, date of discharge/death)POPPI intervention data (for patients recruited at intervention group sites
during the intervention period—IPAT Scores, delivery of stress
support sessions, STAI Score after session 3)

**Table 1 T1:** Patient data collection schedule

	Baseline (at point of recruitment)	End of critical care unit stay	Intervention group sites—during transition and intervention periods			Six months postrecruitment
			Before SSS-I	During sessions	After SSS-III	
Collected inhospital						
Patient details	✓					
Clinical/baseline data	✓					
Critical care unit stay		✓				
IPAT assessment			✓			
SSS delivery				✓		
STAI	✓				✓	
Collected via follow-up questionnaires sent to patients						
PSS-SR						✓
HADS						✓
EQ-5D-5L						✓
Health service and resource use						✓

EQ-5D-5L, EuroQoL Health questionnaire; HADS, Hospital Anxiety and
Depression Scale; IPAT, Intensive care Psychological Assessment Tool;
PSS-SR, Post-traumatic Stress Disorder Symptom Scale - Self Report version;
SSS, stress support session(s); STAI, State-Trait Anxiety Inventory.

Follow-up data (PSS-SR, HADS, EQ-5D-5L, health services and resource use) are
collected via the patient follow-up questionnaire at 6 months postrecruitment.
In addition, data will be linked to CMP and will include demographics,
surgical status, acute severity of illness and duration of organ support, and
duration of critical care unit stay. Support for the collection and use of
patient-identifiable data has been approved for CMP by the Patient Information
Advisory Group (PIAG) under Section 251 of the NHS Act 2006—approval number:
PIAG 2-10(f)/2005. Survival at 6 months will be ascertained through NHS

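### Patient-level adjustment is left to a secondary analysis, so the primary estimate is open to differential recruitment after site randomisation and gives up some precision

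*Protocol article*

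**What the plan says.** All references are to the protocol article.

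- **Primary model (Clinical evaluation).** The PSS-SR at 6 months is analysed by a linear mixed model "including a random effect of site and a fixed effect of period (baseline or" intervention), "adjusted for site-level factors included within the restricted" randomisation algorithm. The Randomisation section gives those factors as geography, teaching status and unit size.
- **Patient-level adjustment (Clinical evaluation).** "A secondary analysis will adjust for prespecified baseline factors associated with" poor psychological outcome, with sedation as the example, and for ability to deliver the "intervention (eg, size of critical care unit, teaching status) at both patient and" site levels. Unit size and teaching status are already randomisation factors, so sedation is the only named covariate that the secondary model adds.
- **Timing of allocation (Randomisation).** In each group of eight, the "individual sites will be randomised (4:4) in their second month of recruitment".
- **Consent (Exclusion criteria, closing text).** The local research team approaches patients. From month 6, patients at intervention sites are offered "the option to provide consent to receive an assessment with IPAT and subsequent" stress support sessions, on top of the common consent to records access and the 6-month questionnaire.
- **Available data (Data collection).** Baseline data include "documented pre-existing anxiety or" depression. The Case Mix Programme linkage adds demographics, surgical status and acute severity.
- **Economic model (Economic evaluation).** It has a random site effect and a "fixed effect of period. The analysis will adjust for prespecified baseline" covariates at patient and site level.

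**The concern.** Randomising sites balances the sites. It does not balance who is approached and who agrees once the allocation is in force. The article does not say in words that recruiters know the allocation. It follows, at the latest from month 6, from the training of the intervention sites and from a consent offer made only there.

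The primary analysis set consists of patients who consented to follow-up, so a change in who consents is a change in who is analysed. The baseline period lets the model allow for stable differences between sites. It cannot separate the treatment effect from a change in case mix that begins in the same arm at the same time.

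Two things are at stake. The headline estimate could carry a recruitment difference in either direction. It would also be less precise than data already collected or linked could make it.

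The planned secondary analysis is only a partial answer, because it does not determine the headline result and because of its named example. Patients enter after more than 48 hours in a unit that, at intervention sites, is meant to have changed its whole environment. Days alive and free from sedation is itself a secondary outcome. Adjusting for sedation before recruitment could therefore remove part of the effect being measured.

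**Working it through.** **1. Reproduce the plan's power.** The inputs come from the two power sections. There are 12 + 12 sites, and alpha is 0.05, taken as two-sided. After the review, SD is 10.8, ICC 0.087 and the effect 4.2, with 12.8 followed-up patients per site in the baseline period and 12.8 (before extension) or 16.5 (after) in the intervention period. The pretrial values are SD 7.5, between-site SD 3, effect 2.9 and 22 patients per site-period.

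With random site, fixed period and treatment only in the second period of the intervention sites, the Hussey-Hughes variance reduces to

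SE² = (2/12) × [v1 − τ⁴/v0], with v0 = τ² + σ²/n0 and v1 = τ² + σ²/n1,

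and power = Φ(effect/SE − 1.96). The SD is read as the within-site SD, because that reading reproduces the stated figures.

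After extension:
- σ² = 10.8² = 116.64; τ² = 116.64 × 0.087/0.913 = 11.11
- v0 = 11.11 + 116.64/12.8 = 20.23; v1 = 11.11 + 116.64/16.5 = 18.18
- SE² = (18.18 − 123.5/20.23)/6 = 2.01, so SE = 1.419
- Power = Φ(4.2/1.419 − 1.96) = Φ(1.00) = 84.1%

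| Stage | SE | Computed power | Stated power |
|---|---|---|---|
| Pretrial | 0.871 | 91.5% | 90% |
| Before extension | 1.534 | 78.2% | 78% |
| After extension | 1.419 | 84.1% | 85% |

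At the upper ICC limit of 0.192 the formula gives 73.1% and 78.7%, matching the stated lower limits of 73% and 79%.

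**2. Precision from patient covariates.** The article gives no R-squared, so the values below are assumptions. σ² is multiplied by (1 − R²) and τ² is held fixed, with 12.8 and 16.5 patients per site.

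| Assumed within-site R² | SE | Power |
|---|---|---|
| 0 | 1.419 | 84.1% |
| 5% | 1.389 | 85.6% |
| 10% | 1.359 | 87.1% |
| 20% | 1.295 | 90.0% |

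**3. Whether the baseline period absorbs the shift.** The estimator is the intervention-period contrast between arms minus a weight times the baseline contrast. The weight is τ²/v0 = 11.11/20.23 = 0.55. A shift confined to the intervention period at intervention sites leaves the baseline contrast unchanged. Nothing is subtracted, and the whole shift passes into the treatment estimate.

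**4. Possible size of the shift.** Suppose recruits differ by d standard deviations on a factor that correlates r with PSS-SR. The shift is then r × 10.8 × d. Both r and d are assumptions.
- r = 0.2, d = 0.1: 0.2 × 10.8 × 0.1 = 0.22 points, or 5% of 4.2
- r = 0.3, d = 0.2: 0.65 points, or 15%
- r = 0.4, d = 0.3: 1.30 points, or 31%

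The sign depends on who becomes more or less willing to consent, which the article cannot tell us.

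**The case against.** The strongest reply is that the plan already contains a patient-adjusted analysis of the same outcome, and that a primary model mirroring the restricted randomisation is a recognised choice rather than an error. This stands in part. A reader might infer that selection bias goes uncorrected throughout the plan. The Clinical evaluation section does not support that, because it prespecifies adjustment at patient level as a secondary analysis. The point concerns which model carries the headline and which covariates are safe to use.

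The design also has safeguards. Core consent is the same in both arms and the extra offer is optional. Sites agree to recruit all eligible patients where possible and to keep a screening and enrolment log, and the process evaluation uses screening and recruitment data. These limit differential consent and allow it to be examined, but they do not exclude it.

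The proposed covariates also fit the likeliest mechanism imperfectly. If distressed patients respond more to an offer of support, the direct collected measure is the STAI at recruitment, which the fix leaves out because it follows exposure to the unit. Documented prior anxiety or depression captures that mechanism only partly. This objection stands, so no claim can be made about how much of any bias would be removed.

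Finally, a design with a stated 85% power is not defective for lack of covariates, and at an R-squared of 5% the gain is small. That is also accepted: precision is a supporting reason. The covariate list may be in the full SAP, and its absence from an article is not criticised here.

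**Conclusion.** The concern holds in a limited form. The stated primary model has no patient-level term, although recruitment follows site randomisation and the consent offer differs by arm from month 6. The baseline period does not protect against a case-mix change that begins with that offer. The economic model, with the same site and period structure, does adjust for patient factors, and the article gives no reason for the difference.

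The documents do not show that selection occurred, which way it would run, or that adjustment would remove it. The range of 0.2 to 1.3 points illustrates assumed values and is not an estimate. The power gain, from about 84% to between 86% and 90%, rests on an assumed within-site R-squared of 5% to 20%, an unchanged between-site variance and a normal approximation with 24 sites. This is a worthwhile improvement to the primary analysis, and the planned model is not invalid without it.

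**What to change.** Before database lock, and before anyone making the decision has seen outcomes by arm:

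1. Add to the primary model a short fixed list of patient factors set before or at unit admission and already collected or linked: age, sex, documented pre-existing anxiety or depression, surgical status and acute severity. Confirm that the severity measure reflects the state at admission, since the article does not give its time window.
2. Leave sedation and STAI at recruitment out of the primary model. If they stay in the secondary model, state that they may already be affected by the intervention.
3. Keep the model with site-level factors only as a supporting analysis and report both.
4. State that adjustment addresses measured factors only, and report baseline characteristics by arm and period so that readers can see any shift in who was recruited.

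The cost is a documented and justified change to the primary analysis of a protocol already at V.2.2, plus a rule for a few missing covariate values. No new data are needed.

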#### Creating a therapeutic environment

Each intervention group site will create a therapeutic environment by encouraging
culture change in their unit. This will be facilitated by ensuring all clinical
critical care unit staff complete the POPPI online training and by teaching and
modelling good communication skills and psychological care at the bedside. The
POPPI online training is an online training course designed to aid the creation of
a calm, less stressful environment by reducing stressors in the environment and
using good communication with patients. The POPPI online training takes
approximately 30 min to complete and comprises five sections (understanding
the stresses of intensive care patients, reducing stress and fear in patients,
communicating with distressed patients, inspiring patients with confidence and
hope, and summary and assessment). Local research teams will enumerate all
clinical critical care staff at the start of the transition period, and then
monthly thereafter to ensure new staff members are registered for the POPPI online
training.

In addition, intervention group sites will ensure that POPPI materials are clearly
displayed (eg, posters) and distributed (eg, pocket cards) throughout the
unit.

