### Power calculation

#### Pretrial power calculation

The power calculation was completed using the approach of Hussey and Hughes
(2007)^33^ to achieve 90% power to detect
a reduction from 6 points to 3.1 points (P<0.05) in the mean PSS-SR at
6 months, and was based on the following assumptions:Mean (6) and SD (7.5) of the PSS-SR were taken from patients in
the feasibility studyEstimated intracluster correlation (ICC) of 0.138—between-site
coefficient of variation 0.5 corresponding to between-site SD of 3
(conservative estimate as no multicentre data available).^42^ Note: the inclusion of a baseline
recruitment period means that the sample size calculation is less
sensitive to the degree of clustering^33^Treatment effect of a reduction of 2.9 points on PSS-SR based on:
reliable change index for the PSS-SR of 8.6 points^43^ being observed in 40% of eligible patients in the
intervention periods assessed as being at high risk of psychological
morbidity using IPAT, with 16% of recruiting patients declining the
interventionHarmonic mean of the number of patients completing follow-up (52 per site
per annum—corresponding to 22 in a 5-month period) based on data
from CMP

With the design and the above assumptions, the estimated total number of patients
recruited (based on CMP data) for the RCT would be 1914 patients from the 24
sites. It is anticipated that 438 will be assessed using IPAT, of which 175 (40%)
will be assessed as being at high risk of psychological morbidity and receive the
stress support sessions.

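### The structural mean model labels as session efficacy an estimate that also absorbs any effect of the unit-wide therapeutic environment, about 3 PSS-SR points per point of environment effect

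*Protocol article*

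**What the plan says.** The Clinical evaluation section of the protocol article adds a further secondary analysis to the intention-to-treat comparisons. It will use structural "mean models with an instrumental variable of allocated treatment to estimate the" "efficacy (adherence-adjusted causal effect) of the stress support sessions among" patients who agree to assessment, are judged high risk and receive sessions. The instrument (allocation), the exposure (the sessions) and the label (efficacy of the sessions) are therefore all fixed in the article.

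The Intervention section lists three elements. The sessions and the relaxation and recovery programme are for patients screened as acutely stressed. The therapeutic environment is not restricted in that way:

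- Creating a therapeutic environment: "Each intervention group site will create a therapeutic environment by encouraging" culture change, with online training for all clinical staff. The training is meant to help produce "a calm, less stressful environment by reducing stressors in the environment and" communicating well with patients.
- Randomisation: sites rather than patients are randomised because it would not be possible "to restrict parts of the intervention to individual patients".
- IPAT assessment and Exclusion criteria: patients scoring below 7 are not referred for sessions, and assessment and sessions are optional at consent. Both groups are still cared for in the changed unit.

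**The concern.** For allocation to be a valid instrument for the sessions, it must affect PSS-SR only through the sessions. Here it has a second route, through trained staff and a calmer unit, which is open to every patient at an intervention site. The feature that made cluster randomisation necessary is the one that undermines this analysis.

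The model credits any benefit from the second route to the roughly one third of patients expected to receive sessions. The two elements differ in what they ask of a unit. The sessions need three selected nurses, a 3-day course, and continuing debriefing and assessment; the environment relies on about 30 minutes of online training plus bedside teaching and displayed materials. A unit choosing between them could be misled if the effect of one is reported as the effect of the other.

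**Working it through.** **Inputs** (Pretrial power calculation)

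- "reliable change index for the PSS-SR of 8.6 points" as the change in a session recipient.
- That change "being observed in 40% of eligible patients in the" intervention periods, being those judged high risk: 0.40.
- An allowance for refusal, "with 16% of recruiting patients declining the" intervention: 1 − 0.16 = 0.84 accept.

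**Step 1. Reproduce the planned effect.** 8.6 × 0.40 × 0.84 = 2.89, which matches the stated 2.9 points. This puts the whole planned effect on session recipients, so the planning model implicitly takes the environment effect as zero.

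**Step 2. Share receiving sessions.** p = 0.40 × 0.84 = 0.336. The stated counts agree: if the 438 assessed are the 84% who accept, there are 438/0.84 = 521 patients, and 175/521 = 0.336.

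**Step 3. What the model estimates.** Express effects as reductions in PSS-SR. Let s be the session effect in recipients and e the environment effect on every patient at an intervention site in the intervention period. Then ITT = p·s + e. With one binary instrument and no sessions in controls, the linear model reduces to

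ITT/p = s + e/p.

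The bias is e/p = e/0.336 = 2.98e. It is additive.

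**Step 4. Size at a true session effect of 8.6**

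| e (points) | Reported | Ratio to 8.6 |
|---|---|---|
| 0 | 8.60 | 1.00 |
| 0.5 | 10.09 | 1.17 |
| 1 | 11.58 | 1.35 |
| 2 | 14.55 | 1.69 |
| 2.9 | 17.23 | 2.00 |

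A simulation agreed, with 24 sites of 200 patients, SD 7.5, no between-site variation and 2,000 repetitions. It gave 8.61 at e = 0 and 11.58 at e = 1.

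**Step 5. Same ITT effect, different explanations.** Hold ITT at 2.9. The model reports 2.9/0.336 = 8.63 however the effect divides. The true session effect is (2.9 − e)/0.336:

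| Share of ITT due to environment | True session effect |
|---|---|
| 0 | 8.63 |
| 25% | 6.47 |
| 50% | 4.32 |
| 100% | 0 |

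The planned analysis cannot tell these rows apart.

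**Step 6. Sensitivity to uptake.** The documents give only the planned share. Over an assumed range of p from 0.20 to 0.50, the factor 1/p runs from 5.0 to 2.0.

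**The case against.** The strongest reply is that the article calls its analysis section an overview and defers to a full analysis plan, where the model form, its assumptions and its sensitivity analyses would normally be set out. That is fair, and it rules out any complaint about missing detail. It does not remove the mismatch, because the instrument and the label are both stated in the article, and following them could give a wrong conclusion about the sessions.

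A second reply is that no document gives an environment effect on 6-month PSS-SR, and the power calculation implies none. This also stands: the bias is conditional. But the protocol includes the environment as an intervention element meant to reduce stress, so zero is an assumption to be declared.

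Several stronger readings are tempting, but the documents do not support them:

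- *The session effect is inflated three-fold.* The bias is about 3 points per point of environment effect. At the planning value one point gives 1.35-fold, and even 2.9 points only doubles the estimate.
- *The exclusion restriction certainly fails and the estimate is biased away from the null.* The restriction fails only if the environment effect is non-zero. The estimate is inflated only if the environment is beneficial. If the sessions were harmful, a helpful environment would pull the estimate toward the null.
- *Recovering 8.6 from 2.9/0.336 shows bias.* It is circular, because 2.9 was built as 8.6 × 0.336.
- *The trial's main result is compromised.* The primary comparison evaluates the whole package and does not use this instrument.

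**Conclusion.** The concern holds in conditional form. The named instrument identifies the session effect only if the therapeutic environment has no separate effect on 6-month PSS-SR. The section does not state this condition, and the intervention is designed to breach it. At the planned uptake, each point of environment effect adds about 3 points to the estimate reported as session efficacy.

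That figure rests on a linear model with a single binary instrument, no sessions in controls, an environment effect equal in recipients and non-recipients, and p = 0.336. The size of the environment effect is unknown from the documents, and so is its direction.

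The relaxation and recovery programme goes to the same stressed patients as the sessions, so it cannot be separated from them either, but it opens no route to non-recipients.

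Severity is moderate: the affected analysis is secondary and the intention-to-treat results are untouched.

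**What to change.** Either of two changes would do.

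1. Relabel the result. Describe it as the effect of the whole package scaled to session recipients (ITT/p), not as the efficacy of the sessions.
2. Keep the session estimand, but state explicitly that it assumes no environment effect. Then report (ITT − d)/p over a pre-specified, plausible range of direct environment effects d, and give the value of d at which the conclusion on the sessions changes.

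The range should be justified on its content. Requiring the conclusion to hold all the way up to d = ITT would be no use, because the session effect is then (ITT − ITT)/p = 0 by construction and no data could pass.

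The cost is some wording and a few extra calculations. The claim about the sessions becomes weaker and less precise.
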